### Subjects

Participants (male and female) between 18 and 65 years of age who underwent bariatric surgery (sleeve gastrectomy and gastric bypass) at least 12 months and not more than 20 months previously will be recruited. This timeframe is used to anticipate the period when patients appear to be at risk of weight regain (12–24 months postoperatively) [2] and when they need help coping with lifestyle adjustments.

For the purpose of this study, patients who initially lost weight successfully after surgery will be included. We seek to exclude potential medical or surgical problems that are not related to lifestyle and psychological adjustment and that could be implicated in and limiting to the initial weight loss. Furthermore, given that our ultimate objective is to prevent weight regain, significant initial weight loss is required. Significant weight loss will be considered when the percentage of excessive weight loss is higher than 30. Furthermore, participants who present with significant weight regain (more than 15 % of the total weight loss) since the nadir weight at the time of registration will be excluded. Other specific exclusion criteria include the following:No regular internet access;Inability to read and understand Portuguese instructions;Lack of willingness to have or create an email account;Presence of an active psychiatric disorder (e.g., bipolar disorder, psychotic disorder, suicidal ideation, eating disorders);Intake of weight-affecting drugs;Concomitant weight loss treatment besides treatment as usual;Pregnancy or lactation.

### Proposed sample size and power calculations

The sample size was computed by considering a 0.2 effect size, an alpha level of 0.05, a desired statistical power of 0.8, four predictors or measures and a 20 % dropout rate; this calculation suggested that a total of 180 participants should be recruited (90 in each group).

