### Statistics

Pearson’s chi-square tests will be used to analyze significant differences in the proportion of cases with weight regain and in specific outcome variables between the intervention group and the control group. Significant weight regain will be considered when higher than 5 kg. The Kaplan–Meier approach (together with the log-rank test) will be used to answer the main question of efficacy. Repeated-measures analysis of variance (ANOVA) will be conducted to explore differences between the participant groups for different key variables at various time points. The main effect for surgery type will be investigated. Variables such as log-in frequency, task submission, satisfaction with the program, socio-demographics, pre-intervention scores on self-report measures, and time since surgery will be tested as covariates and predictors of outcomes using Cox regression models. Relevant baseline differences will be included as covariates. Hierarchical linear models will be used to investigate different trajectories of relevant variables assessed from *T*_b_ to *T*_fu12._ Hierarchical linear models are the models that best fit unbalanced designs with unequal number of observations (missing data) per subject. Self-report measures (for depression, impulsiveness, eating disorder and eating patterns, body image, and general distress) will be examined by conducting an analysis of covariance to explore interference with weight outcomes. Post-hoc comparisons will be conducted using Tukey’s procedure. Controlled effect sizes will be calculated using the Cohen’s *d* statistic.

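### The 80% power statement is not a calculation for the log-rank test that is to answer the main efficacy question

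*Protocol article*

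**What the plan says.** Under Proposed sample size and power calculations, the protocol article says: "The sample size was computed by considering a 0.2 effect size, an alpha level of 0.05, a desired statistical power of 0.8". The same sentence brings in "four predictors or measures", allows for one participant in five dropping out, and arrives at 180 participants, 90 per group. The section names no test, no effect-size metric, no sidedness and no within-person correlation.

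Under Statistics, the Kaplan–Meier approach and the "log-rank test) will be used to answer the main question of efficacy". Significant regain is set at more than 5 kg. Chi-square tests are listed for the proportion with regain. Repeated-measures ANOVA is given an exploratory role. Cohen's d is the only effect-size metric the article names, and it is named for reporting results ("Controlled effect sizes will be calculated using the"…), not for the sample size.

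Under Primary and secondary outcome measures, weight regain is assessed at four times: baseline, end of treatment, and 6 and 12 months of follow-up.

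The Background cites long-term regain of about 30%, possibly as high as 97%, and about 37% for regain of more than 25% of the weight lost. Neither the 30% nor the 37% is a rate for regain above 5 kg.

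**The concern.** The inputs to the power statement have no place in a log-rank calculation. An unlabelled standardised effect and a count of predictors or measures belong to a regression or a repeated-measures ANOVA. A log-rank calculation needs a hazard ratio and expected events, and the article gives neither for the 5 kg threshold. The stated 80% therefore belongs to some other analysis, while the log-rank test carries the efficacy conclusion.

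This matters when the result is read. With 80% power on record, a non-significant log-rank test invites the conclusion that the programme does not work. Whether that is fair depends on how many participants pass 5 kg, which the plan does not address.

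**Working it through.** **1. What the inputs can reproduce.** Evaluable after dropout: 180 × 0.8 = 144, or 72 per arm. All results use two-sided alpha 0.05, which is assumed because sidedness is not stated.

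*Repeated measures, between-group effect.* With m = 4 and f = 0.2, the noncentrality is λ = N f² m / (1 + (m − 1)ρ) on 1 and N − 2 degrees of freedom. For N = 144 and ρ = 0.63, λ = 144 × 0.04 × 4 / 2.89 = 7.97 and power is 80%. So 144 / 0.8 = 180 is recovered at a correlation of about 0.63. Power at other correlations is 85% at 0.5, 77% at 0.7, 73% at 0.8 and 70% at 0.9.

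*Regression with four predictors, f² = 0.2.* This needs 65 in total. With 144, power is 99.5%.

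*Single-time-point readings:*

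| Reading of 0.2 | Evaluable N for 80% power | Power with 144 |
|---|---|---|
| Cohen's d (t test) | 394 per group | 22% |
| Cohen's f, i.e. d = 0.4 | 100 per group | 66% |
| w (chi-square, 1 df) | 197 in total | 67% |

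The sentence as written is compatible with anything from 65 to 788 (2 × 394) evaluable participants. Some readings support 144 and some do not.

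**2. What 180 gives for the log-rank test.** Schoenfeld's formula for 1:1 allocation gives the events required:

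D = 4 (1.960 + 0.842)² / (ln HR)² = 31.40 / (ln HR)².

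Expected events with n per arm and control event proportion p_C, under proportional hazards:

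D = n (p_C + p_T), where p_T = 1 − (1 − p_C)^HR.

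Setting the two equal gives the detectable HR. For n = 72 and p_C = 0.37, HR = 0.408. Then p_T = 1 − 0.63^0.408 = 0.172, expected events are 72 × (0.37 + 0.172) = 39.0, and required events are also 39.0.

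Two values of n bound the answer. The lower, 72 per arm, counts completers only at the planned 20% dropout. The upper, 90 per arm, treats everyone as fully followed. People who drop out contribute until they are censored, so the truth lies between.

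| Assumed control proportion with regain > 5 kg | HR for 80% power, 72 per arm | HR for 80% power, 90 per arm |
|---|---|---|
| 30% | 0.361 | 0.409 |
| 37% | 0.408 | 0.454 |
| 50% | 0.473 | 0.517 |
| 70% | 0.545 | 0.584 |

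Power at fixed hazard ratios, as 72 to 90 per arm:

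| Control proportion | HR 0.5 | HR 0.6 | HR 0.7 |
|---|---|---|---|
| 30% | 52–61% | 33–40% | 19–23% |
| 37% | 61–70% | 40–47% | 23–27% |
| 50% | 75–83% | 51–60% | 30–36% |
| 70% | 88–94% | 67–76% | 40–48% |

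Every control proportion here is an assumption. The 30% and 37% are borrowed from the Background figures for other definitions of regain. The 50% and 70% extend the range upward.

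**The case against.** The strongest reply is that 180 is a sensible number honestly derived. The phrase "four predictors or measures" fits the four assessments of the primary outcome, and a repeated-measures calculation with f = 0.2 and a plausible correlation returns 144, hence 180. On the other word in that phrase, predictors, a regression with f² = 0.2 is amply powered. A reader might infer from the low power for d, f or w that 180 is an arithmetic error, or that it fails on every usual reading. The documents do not support this. The d reading in particular borrows a metric that the article names only for reporting. This part of the reply stands.

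A second reply is that a condensed article may leave the metric and the correlation to the full protocol or analysis plan. That also stands, and their absence is not the finding here. The finding is that the article states a power figure and names a main test, and the first is not for the second. The sample size section names no test, so this is an inference, but a strong one: nothing in it is a time-to-event quantity.

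A third reply is that the log-rank figures rest on an unknown event rate. They do. A reader might conclude that the trial could detect only a very large effect. At control proportions of 30–37% that is a fair description, but at 70% a hazard ratio of 0.5 already has 88–94% power, and the Background allows for regain rates above that. The documents do not settle which applies.

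**Conclusion.** The 80% power cannot be claimed for the log-rank test named for the main efficacy question, because no hazard ratio, event rate or event count for regain above 5 kg underlies it. This follows from the text and needs no assumption about the event rate.

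The size of the gap does need one. With 72 to 90 per arm, 80% log-rank power requires a hazard ratio of about 0.36–0.41 at 30% control events, 0.41–0.45 at 37%, 0.47–0.52 at 50%, and 0.545–0.584 at 70%. These figures assume proportional hazards, two-sided alpha 0.05, Schoenfeld's approximation and dropout no worse than the planned 20%.

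The recruitment target is not shown to be wrong. The defect is a mismatch between the power statement and the main test.

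**What to change.** Keep 180. Add a power statement for the log-rank test, for example: with 72 (completers only) to 90 (full follow-up) per arm and two-sided alpha 0.05, 80% power corresponds to a hazard ratio of 0.36–0.41, 0.41–0.45, 0.47–0.52 or 0.545–0.584 if 30%, 37%, 50% or 70% of controls regain more than 5 kg. Label these proportions as assumptions and say that the Background figures of 30% and 37% are not for the 5 kg threshold. If the sponsor has data on that threshold, use them to narrow the range.

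State which analysis the 0.2 calculation belongs to. If it was repeated measures or regression, say so and give the metric, plus the correlation where one was used.

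The cost is wording only. No extra participants are needed, but the power quoted for the main question becomes less favourable over much of the plausible range.

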### Assessment

Figure 1 depicts the time flow and assessment times for this project.

**Fig. 1 Fig1:**
[figure not shown]
Flow chart of the assessment times of the study protocol. FMS, feedback messaging system; *T*
_b_, baseline assessment_;_
*T*
_m4_, 4-month midterm assessment; *T*
_m8_, 8-month midterm assessment; *T*
_f_, final (end of treatment) assessment; *T*
_fu6_, 6-month follow-up assessment; *T*
_fu12_, 12-month follow-up assessment

#### Anthropometric measures

Participants will be instructed to report their weight based on a standardized assessment self-reported using the same scale on the same day of the week under the same conditions (the time of day and without clothes). The program will ask participants to report their weight once a month in one of their weekly assessments as part of their self-monitoring tasks. Both the intervention group and the control group will have their height and weight measured by the research team at baseline (*T*_b_), at 4- and 8-months midterm assessment (*T*_m4_, *T*_m8_), at the end of the intervention (final; T_*f*_), and at 6- and 12-months follow-up (*T*_fu6_, *T*_fu12_). The weight history of participants (e.g., highest and lowest weight since adulthood, pre-surgery weight, and lowest weight since surgery) will be self-reported.

#### Self-report questionnaires

##### Sociodemographic and weight history

This history assesses data on the demographic information (sex, age, and marital status) and relevant clinical variables (type of surgery, pre-surgery weight, lowest and highest weight before surgery, lowest weight achieved after surgery).

##### Clinical inventory

This inventory assesses the history of psychological/psychiatric disorders, current medications and other current psychiatric or psychological disorders, as well as alcohol use.

### Psychological self-report measures

Repetitive Eating Questionnaire [12]: This self-report questionnaire assesses a grazing-type eating pattern through 15 items, resulting in two subscales that reflect compulsive grazing and non-compulsive grazing subtypes.

Depression Anxiety Stress Scales [36]: This 21-item questionnaire generates subscales on depression, anxiety, and stress.

Eating Disorder – 15 [37]: This 15-item questionnaire assesses eating disorder cognition and behaviors, with subscales for weight and shape concerns and for eating concerns.

Negative Urgency Subscale [38]: This 12-item scale assesses an individual’s tendency to surrender to strong impulses, particularly when accompanied by negative emotions, such as depression, anxiety, or anger.

Influence of weight: Developed by the research team, this 12-item measure inquires about the influence of weight in different areas of life (e.g., intimate relationships, professional roles, self-esteem).

Satisfaction questionnaire: Developed by the research team, this 19-item questionnaire addresses the utility and feasibility of the program from the patient’s perspective.

All questionnaires have been used with this sample by the research team in previous studies, and show good internal consistency for use with bariatric surgery patients.

Table 3 presents a summary of the self-report measures used for each group at each assessment time.

**Table 3 Tab3:** Timeline for the self-report measures

	Registration	Baseline (*T* _b_)	4-month midterm assessment (*T* _m4_)	8-month midterm assessment (*T* _m8_)	Final (end of treatment) assessment (*T* _f_)	6-month follow-up assessment (*T* _fu6_)	12-month follow-up assessment (*T* _fu12_)	Weekly
Sociodemographic weight history	X	–	–	–	–	–	–	–
Clinical inventory	–	X	X	X	X	X	X	–
Repetitive Eating Questionnaire [12]	–	X	X	X	X	X	X	–
Depression Anxiety Stress Scales [36]	–	X	X	X	X	X	X	–
Eating Disorder – 15 [37]	–	X	X	X	X	X	X	–
Negative Urgency Subscale [38]	–	X	X	X	X	X	X	–
Influence of weight	–	X	X	X	X	X	X	–
Satisfaction questionnaire	–	–	–	–	Intervention group	–	–	–
Eating and exercise behaviors (Table 4)	–	Control group	Control group	Control group	Control group	X	X	Intervention group

*X* available for both intervention and control group

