### Intervention strategy of APOLO-Bari – the rationale

After initial and dramatic weight change, patients can consolidate and build on their new and healthy lifestyles during the postoperative period. Handling post-surgery demands implies the need for behavioral modifications to engage in a healthy lifestyle and to comply with prescribed nutrition guidelines, especially at later follow-up times. However, as the follow-up time increases, the number of consultations with the medical team invariably decreases, resulting in a gap between health services and patients, particularly patients who might not otherwise have access to specialized treatment because of a lack of available resources outside of urban centers. With less frequent medical appointments over time, problematic behaviors might be overlooked and might not be clinically addressed, resulting in eventual weight regain.

The novelty and strength of the program APOLO-Bari are based on the ability to monitor key patient features related to outcomes continuously, to support and guide patients continuously, and to provide cognitive-behavioral-based support during the follow-up period, either to improve results or prevent poor outcomes. This approach attempts to narrow the gap between clinical services and patients by providing long-distance support to a large number of patients simultaneously, without the need for face-to-face sessions.

However, the disadvantages of internet-based programs have been noted; hence, the feasibility of the widespread utilization of such programs is called into question: weak adherence through the minimal use of internet resources, high rates of attrition, less education and less initial weight loss have been associated with dropout rates. In contrast, various studies have shown a positive association between log-in frequency and weight loss [30]. To overcome some of these difficulties, APOLO-Bari includes interactive tools that are designed to enhance adherence to the program, such as a feedback messaging system that is based on the patient’s input and a privileged channel (chat sessions) to contact a professional directly with specific concerns.

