Furthermore, the server will send a motivational message directly when a participant has missed a weekly assessment or has not logged in for more than a month. The system will automatically send an email (‘case alarm’) to the research team when a participant reports symptoms that require additional clinical attention: (i) weight regain of >5 kg over the previous 3 months and (ii) the presence of any risk behaviors every week for at least 3 months. In such a case, the research team will contact the participant via email.

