## Objectives of the study and expected outcomes

The specific objectives of this project are the following:To test the short- and long-term efficacy of the program in preventing weight regain and promoting weight loss maintenance, promoting new eating behaviors, decreasing psychological distress, enhancing individual self-concept, and addressing other psychological outcomes.To test the utility, feasibility, and perceived satisfaction with APOLO-Bari in terms of compliance with proposed tasks, log-in frequency, and direct evaluation of the satisfaction of participants. Participants with higher log-in frequency and compliance with monthly assessments are expected to report better weight outcomes, higher levels of satisfaction with weight loss and surgical treatment, and lower scores on the self-reported measures, thus reflecting better psychosocial functioning.To study weight regain by exploring the temporal courses of eating-related features and predictors of weight regain. We expect to identify fluctuations in key behaviors that precede weight regain.

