### Informed consent and randomization

Those who agree to participate in the study will have a computer connected to the internet, and each participant will complete the informed consent form online and register in the program by creating a personal username and password. All participants will complete an initial short sociodemographic and clinical questionnaire (see details in the measures section). To ensure concealment of allocation, the APOLO-Bari system will then automatically randomize (computer-generating random numbers) the participants on a 1:1 basis, matching for age, sex, and surgery type.

After randomization, intervention group members will receive full access to the three components of the APOLO-Bari program in their personal accounts. The intervention will last for 12 months, and a 6-month period will follow, with no program access possible. During the intervention period, the system will record data on log-in frequency, task submission, and weekly monitoring from the intervention group.

The control group will only have access to general information on obesity and bariatric surgery and to the set of self-report measures at the different assessment times. The control group participants will be informed of the assessment times and the possibility of accessing the full program after the study is complete. Both groups will receive reminder emails every time a questionnaire or activity is available.

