### Blinding and data access

Intervention and assessment are conducted exclusively in the APOLO-Bari program. The psychologist participating in the interactive chat sessions does not have access to the program information submitted by the participant. The statistician conducting the statistical analysis has not been involved in the implementation of the program. Treatment allocation has not been previously disclosed to the statistician.

Only the principal investigator and the statistician will have access to the final trial dataset. This is stated in the information for the participant sheet submitted to the ethical committee approval.

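### Satisfaction with the program is rated once, at end of treatment and through the program itself, so the self-rated part of the utility objective probably over-represents participants still engaged at month 12

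*Protocol article*

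**What the plan says.** The second objective in the protocol article is "To test the utility, feasibility, and perceived satisfaction with APOLO-Bari", to be judged "in terms of compliance with proposed tasks, log-in frequency, and direct evaluation of the satisfaction of participants". It therefore has three parts: two measures of use and one self-rating. The abstract also puts perceived utility, next to efficacy, in the primary purpose.

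The self-rating comes from the satisfaction questionnaire (Psychological self-report measures): "this 19-item questionnaire addresses the utility and feasibility of the program". Its row in Table 3 reads "Satisfaction questionnaire – – – – Intervention group", which places it at T_f only. The columns for months 4 and 8 hold a dash, as do both follow-up columns and the weekly column.

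The other two parts have a different source. Under Informed consent and randomization, during the intervention period "the system will record data on log-in frequency, task submission, and weekly monitoring from the intervention group".

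On delivery, Blinding and data access states: "Intervention and assessment are conducted exclusively in the APOLO-Bari program". The rationale section names "weak adherence through the minimal use of internet resources, high rates of attrition" among the known disadvantages of internet programs, and the sample size section allows for 20% dropout. The system already reacts when a participant "has not logged in for more than a month", but the only response described is a motivational message.

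Finally, the Statistics section lists satisfaction with the program among the variables to be tested as covariates and predictors of outcome in Cox regression models.

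**The concern.** A rating collected once, at month 12, through the tool being rated, depends on who is still using that tool. Participants who found the program unhelpful are more likely to have stopped logging in, and so less likely to see or answer the form. The retention voucher does not offset this: it requires at least 70% of assessments, so someone already below that level gains nothing financially by completing T_f.

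Two results are at stake. The first is the reported level of satisfaction and perceived utility, which would probably be too favourable. No analysis plan can recover ratings that were never requested. The second is the use of satisfaction as a predictor in Cox models. A rating at T_f is missing for those who have left, and for everyone else it is made after any regain during the 12 months of treatment. Regain may then have shaped the rating, instead of the rating predicting regain.

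**Working it through.** The article states no expected satisfaction rate or response rate, so there is no figure of the plan's own to reproduce. The check has two parts.

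**1. Size of a possible non-response bias**

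From the sample size section: 90 participants in the intervention group and 20% dropout. Assumptions, none of them in the documents:
- the 20% applies to this arm and to this questionnaire at T_f;
- 85% of respondents are satisfied;
- between 30% and 60% of those who do not answer would have been satisfied.

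Respondents: 90 × 0.80 = 72. Not answering: 90 × 0.20 = 18.

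With m the share not answering, p_r the satisfied share among respondents and p_n the satisfied share among the others:

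- share among all randomised = (1 − m) × p_r + m × p_n
- overstatement by the T_f figure = m × (p_r − p_n)

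| m | p_n | Share among all 90 | Overstatement |
|---|---|---|---|
| 20% | 60% | 0.8 × 0.85 + 0.2 × 0.60 = 80% | 5 points |
| 20% | 30% | 0.8 × 0.85 + 0.2 × 0.30 = 74% | 11 points |
| 30% | 60% | 0.7 × 0.85 + 0.3 × 0.60 = 77.5% | 7.5 points |
| 30% | 30% | 0.7 × 0.85 + 0.3 × 0.30 = 68.5% | 16.5 points |

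Without any assumption about p_n, the share among all 90 lies between (1 − m) × p_r and (1 − m) × p_r + m:

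- m = 10%: 0.9 × 0.85 = 76.5%, up to 86.5%
- m = 20%: 0.8 × 0.85 = 68%, up to 88%
- m = 40%: 0.6 × 0.85 = 51%, up to 91%

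The bounds lie on both sides of 85%, so upward bias is not a mathematical certainty. It is the likely direction, because disengagement and dissatisfaction tend to go together.

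**2. Timing of satisfaction as a predictor**

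| Assessment | Weight measured by the team | Satisfaction rating already available |
|---|---|---|
| Month 4 (T_m4) | yes | no |
| Month 8 (T_m8) | yes | no |
| Month 12 (T_f) | yes | made at the same assessment |
| 6- and 12-month follow-up | yes | yes, if T_f was answered |

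Only regain first seen after T_f can be preceded by a satisfaction rating. For regain during treatment, the order of cause and effect cannot be read from the data as scheduled.

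**The case against.** The strongest case against the point has four parts.

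- **Nobody is excluded.** A reader might infer from Table 3 that early stoppers are left out and that the whole objective is answered from completers. The documents do not support this. The table assigns the form to the intervention group, not to active users, and stopping use is not the same as missing T_f. The team measures weight in both groups at T_f, holds two contacts per participant and sends reminders. Two of the objective's three parts are recorded by the system throughout, so early stoppers contribute to them. This stands: the problem is a risk of selective non-response in one part.
- **Log-in frequency and satisfaction.** A reader might also infer that the planned link between the two loses its low-use end. The objectives section links log-in frequency to satisfaction with weight loss and surgical treatment, not with the program, so that consequence does not follow.
- **The size is hypothetical.** The 20% is a trial-wide allowance with no arm or time point, and no satisfaction rate is given. This stands; the figures above are illustrations only.
- **A single rating at the end is a legitimate choice, and missing forms may be dealt with in a fuller document.** This stands in part. A plan not shown here may well cover response rates and missing questionnaires. But the collection schedule is fixed in the article, and no later analysis can supply ratings that were not collected.

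**Conclusion.** The point holds as a minor one. Self-rated satisfaction and utility rest on one T_f questionnaire delivered through the program, and the result is likely to over-represent participants still engaged at month 12. Under the assumptions shown, the overstatement is 5 to 11 points with 20% not answering and 7.5 to 16.5 points with 30%; the true size cannot be known from the documents. It rests on two premises: that questionnaires are answered in the program, as the article says, and that those who disengage are on average less satisfied, which is plausible but not documented.

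The use of satisfaction as a Cox predictor has a separate timing problem, which does not depend on the amount of non-response: for regain during treatment, the rating comes too late to be a predictor.

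The log-in and task-compliance results, the comparison of weight between groups and the sample size are unaffected.

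**What to change.** **Collection**
- Also give the questionnaire, or a short subset of it, to the intervention group at months 4 and 8, when they already complete the clinical inventory and five psychological measures.
- Send an optional short form, with reason for stopping, when a participant withdraws or when the existing trigger for a month without log-in fires. It must be optional because participants may withdraw without giving a reason.

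**Analysis and reporting**
- Keep the T_f rating as the main satisfaction result. Earlier ratings refer to a shorter period of use and should not be merged with it.
- Report the number answering at T_f out of all randomised intervention participants.
- Compare those who answer with those who do not on the log-in data already recorded.
- Show the earlier or exit ratings of participants missing at T_f as a sensitivity analysis.
- Where satisfaction is a predictor of regain, use only ratings made before the event.

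**Cost.** Two extra short administrations and one automatic form, in a system that already sends reminders and messages. Questionnaire burden rises slightly, some participants will not answer the exit form either, and the satisfaction figure may be less favourable. The article reports that recruitment is not complete, so the added forms could still reach participants. If collection cannot be changed, the response count and the comparison on log-in data need no new instrument.
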